## Abstract

**Introduction:**

When physical activity contains training of at least three components such as balance, coordination and strength, among others, it is called multicomponent training. This type of training is recommended for improving the functional capacity in elderly individuals but has no lasting effects. The association of transcranial direct current stimulation (tDCS) with other types of therapy has been shown to facilitate the enhancement and prolongation of therapy outcomes.

**Aim:**

The objective of this study is to evaluate the effect of multicomponent training associated with active or sham tDCS on the performance of functional capacity in the elderly before treatment, after treatment and 30 days after the end of treatment. The secondary objective will be to correlate the performance of the primary outcome (functional capacity assessed by the Glittre Daily Life Activity Test) with walking capacity (by 6-min walk test), balance (with the mini-Balance Evaluation Systems Test), functional independence (by the Functional Independence Measure) and quality of life (with the World Health Organization Quality of Life Instrument).

**Methods:**

Twenty-eight elderly people from the community will participate in the study, and will be randomized into two groups: 1) multicomponent training associated with active tDCS; and 2) multicomponent training associated with sham tDCS. The multicomponent training sessions will be held twice a week for 12 weeks, totaling 24 sessions. The tDCS will be administered over the dominant dorsolateral prefrontal cortex at the same time as multicomponent training, with an intensity of 2 mA, for 20 min. The evaluations will be made pretraining, after 24 training sessions and 30 days after the end of the training.

**Discussion:**

We hypothesize that tDCS, when associated with multicomponent training, can potentiate and prolong the effects of this training on the functional capacity of the elderly. If this hypothesis is confirmed, this protocol may contribute to a longer-lasting physical rehabilitation of the elderly, encouraging them to maintain their independent daily activities for longer.

**Trial registration:**

The study was registered in the Brazilian Clinical Trial Registry (RBR-2crd42) and received approval from the Human Research Ethics Committee of University Nove de Julho, São Paulo, Brazil (process number 3.077.953).

## Introduction

The World Health Organization (WHO) defines older adults as individuals with a chronological age equal to or more than 60 years in developing countries and 65 years in developed countries [1]. It is estimated that the population of older adults will number approximately 1.2 billion by the year 2025 and will increase to approximately two billion by the year 2050 [1, 2]. In Brazil, the number of older adults is expected to reach approximately 300 million by the year 2050 [3]. Therefore, one of the goals of the Health Ministry in Brazil is to create strategies to address the needs of this growing population so that older adults can age with health, functional independence and quality of life [4].

Functional independence refers to the ability to perform functional activities without the need for other people. This requires the individual to have security to walk, strong muscles, balance, motor coordination, and flexibility. These skills can be enhanced by engaging in daily physical activity through exercise programs, such as multi-component training recommended for seniors by the American College of Sports Medicine [5–12] and involving the training of at least three of these features (or components) in a single session [5–12].

Multicomponent training is effective for improving functional capacity and improving the performance of activities of daily living [13]. However, to observe these effects, prolonged training of 3 to 6 months is required. This time is needed for neurophysiological changes, such as the release of brain-derived neurotrophic factor, to become apparent. However, once this training is stopped, the effects do not last long [14].

Studies with transcranial direct current stimulation (tDCS) [15–21] combined with motor and cognitive therapies have shown that this technique is capable of stimulating neuroplasticity and facilitating motor learning [22], increasing and prolonging the effects of different therapies [23].

tDCS is a neuromodulatory technique that induces excitability of the cerebral cortex without inducing action potential and can modify the resting potential of the neuronal membrane, consequently modulating the neuronal firing rate [23]. It consists of the application of a lowintensity electric current in specific regions properly measured under the scalp using two electrodes that act on the balance of ions inside and outside the neural membrane, stimulating changes in the resting threshold [23]. Anodic current increases cortical excitability, favoring membrane depolarization, and cathodic current decreases cortical excitability, favoring membrane hyperpolarization [20, 21].

Based on this information, this study hypothesizes that tDCS is capable of enhancing and prolonging the effects of multicomponent training on the functional capacity of the elderly, making this type of physical training more effective.

### Objectives

The main objective of this study will be to evaluate the functional capacity of the elderly participants before and after participation in physical activity with multicomponent training associated with active or sham tDCS and to verify if these results are maintained 30 days after the end of the training.

Secondary outcomes will correlate the performance of the primary outcome (functional capacity) with the walking capacity, balance, muscle strength and functional independence after multicomponent training alone or when associated with tDCS.

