### Allocation and blindness

The NeuroConn DC-STIMULATOR PLUS device has settings that allow one to select the active or sham protocol by codes consisting of a five-digit numeric sequence (provided by the manufacturer). There are 200 different possibilities (100 for each stimulus type of active or sham), so each participant will have their own code. Access to these numbers will only be provided for one of the researchers (researcher 1). This researcher will randomize the participants (http://www.randomization.com) and enter the codes according to the randomization (active group or sham) into the equipment, and thus it is not possible for the researcher who will apply the treatment and evaluate the results (researcher 2) to know the code and what is the treatment, ensuring blinding.

To ensure blinding of the participants and researcher 2 (a double-blind study) during stimulation, the device will appear switched on for both protocols (with no different external visual cues); however, for the active protocol the device will be programmed to operate for 20 min. For the sham protocol, the device will emit current for 20 s and then reduce this to zero (this programming is done by the manufacturer).

Researcher 2 will explain to the participant that they may feel a slight tingling that may continue or subside over time.

When treatment is over, researcher 1 will give researcher 2 a table for data analysis, with the names of participants divided into groups 1 and 2 (according to randomization), without treatment identification.

Researcher 2 will only know which group has received active and which group has received sham tDCS when the 30-day follow-up statistical analyses are complete.

To check blinding to treatment, a questionnaire will be delivered to each participant and researcher 2 at the end of each session asking whether the treatment was applied as active or sham tDCS.

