#### Assessment of functional capacity

To assess functional capacity, the Glitter-ADL test [31] will be used at three points (pretraining, post-training and 30 days after the end of training). T's an instrument validated for patients with chronic obstructive pulmonary disease, with acceptable reliability (95% CI −0.20 to −0.54).

The Glittre-ADL test is an instrument validated for patients with chronic obstructive pulmonary disease, with acceptable reliability (95% CI −0.20 to −0.54) [31], which has been previously tested in healthy older adults [38, 39], showing excellent intra-rater (ICC 0.90, 95% CI 0.86–0.93) and inter-rater (ICC 0.91, 95% CI 0.88–0.94) reliability (*P* < 0.001 for both). The intra-rater standard measurement error was 0.03 min and the inter-rater standard measurement error was 0.05 min. The minimal detectable change for intra-rater was 0.40 min and for inter-rater was 0.07 min.

The Glittre-ADL test consists of getting up from a chair with a backpack containing one weight (2.5 kg for women and 5.0 kg for men), walking 5 m on a flat track, going up and down steps measuring 17 cm in height and 27 cm in depth, and walking another 5 m to a set of three shelves, one at the top (at shoulder level), one in the middle (at pelvic waist level) and one at floor level. When reaching the shelves, the participant should transfer three balls, weighing 1 kg each, from the top to the middle and then to the bottom shelf and finally from the bottom shelf to the floor, and then return the balls in the same sequence until they reach the upper shelf. The task should be repeated in the reverse sequence until the participant is sitting again.

The complete test consists of five repetitions of this circuit, which should be performed as quickly as possible. Performance is given by the running time (in minutes) of the five laps with a shorter the time indicating better performance, considering a clinically important improvement between 7 and 40 s [38]. To be considered as preserved functional capacity, the test must be performed in approximately 2 min [39].

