##### Data analysis

To identify data normality and cases of non-normal distribution, data distribution analyses will be performed by visual analysis of the histograms of each treatment group. Descriptive statistics will be used as measures of central tendency and dispersion, mean and standard deviation will be used for quantitative variables, frequency will be used for categorical variables and the median and the interquartile range will be used for nonparametric variables.

An ANOVA of two factors followed by the Bonferroni test will be used for comparative analysis between groups (active and sham tDCS) along the time points (pre- and post-training).

A *P* value <0.05 will be considered indicative of statistical significance, and Pearson correlation will be used to calculate the relationship between Glittre-ADL performance and the secondary outcomes of the capacity to walk (6MWT), balance (mini-BESTest), FIM, instrumental activities of daily living, quality of life, and evaluation of muscle strength at pretraining, following treatment and at 30-day follow-up.

Individual results will be analyzed later for each outcome. These individual data will be an important complement to identifying the clinical relevance of the results [42].

Clinical characteristics, especially outcome-related characteristics, and functional capacity (Glittre-ADL test) will be compared at baseline to ensure homogeneity of the groups. The significance level of *P* < 0.05 refers to the alpha risk adopted in the ANOVA test. If there is a significant difference between groups, times, or interactions between groups and time, the *P* value of the multiple comparison analysis from the Bonferroni post-hoc test will be adopted.

All analyses will be processed using the SPSS program (IBM SPSS Statistics for Windows, Version 22.0, released in 2013, IBM Corp., Armonk, NY, USA). In case of dropouts and missing data, an intention-to-treat analysis will be performed using the appropriate imputation method according to the missing standard, the data will be analyzed when participants receive no treatment (or are under a control condition) depending on the group assigned, and when outcome measures are available an analysis will be performed as if the individuals had received the treatment (or a control condition).

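### Maintenance at 30 days is part of the main objective, but the stated tests look only for differences, and non-significance with 14 per arm cannot show that the gain was kept

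*Protocol article*

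**What the plan says.** The Objectives section sets out to compare functional capacity before and after training with active or sham tDCS and, in the same sentence, "to verify if these results are maintained 30 days after the end of the training". The Introduction gives the hypothesis: "tDCS is capable of enhancing and prolonging the effects of multicomponent training". The Abstract, Outcomes and Assessment of functional capacity sections all schedule the Glittre-ADL test at pretraining, after the 24 sessions and 30 days after the end of training.

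The Data analysis section gives this method: "An ANOVA of two factors followed by the Bonferroni test will be used for comparative analysis between groups", taken "along the time points (pre- and post-training"). If a group, time or interaction effect is significant, "the *P* value of the multiple comparison analysis from the Bonferroni post-hoc test will be adopted". Individual results are to be examined as a complement, without a decision rule. The article attaches no margin, confidence interval or other criterion to maintenance.

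Two other places bear on the point. Allocation and blindness says that unblinding comes "when the 30-day follow-up statistical analyses are complete", so some 30-day analysis is intended, but its form is not given. Assessment of functional capacity describes Glittre-ADL scoring as "considering a clinically important improvement between 7 and 40 s". That range is stated for improvement and is not linked to loss.

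**The concern.** To say that a result was maintained is to say that no relevant part of it was lost. A difference test answers another question. If the post-training versus 30-day comparison is significant, loss has been shown. If it is not, either little was lost or the trial was too small to see the loss. A significant pretraining versus 30-day comparison does not settle the matter either: it shows that some gain remains, not that the gain was kept.

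If non-significance came to be taken as maintenance, the error would run in favour of the trial's hypothesis. The fewer the participants and the more the dropouts, the easier it would be to conclude that the effect lasted. Adding the 30-day visit to the ANOVA would repair the omission of that visit, but would still leave maintenance without a criterion.

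**Working it through.** **The plan's own figure.** The pilot means are 172.05 s and 203.82 s with SD 30.79 s (Sample size calculation). The difference is 31.77 s, so f = 31.77/(2 × 30.79) = 0.516. I used the repeated-measures between-groups F test with three measurements and an assumed correlation of 0.5. With N = 22, λ = f² × N × 3/(1 + 2 × 0.5) = 0.2662 × 22 × 3/2 = 8.78, and power is 0.805. Allowing for 20% dropout, 22/0.8 = 27.5, which rounds to 28. The stated 22 and 28 are reproduced. On this basis the size rests on a between-group effect averaged over visits, not on a question about maintenance.

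**Power to see a loss between post-training and 30 days.**

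Inputs:
- SD 30.79 s, taken as equal at each visit (Sample size calculation; equality is an assumption).
- Between-visit correlation r = 0.5 to 0.9 (assumed; not given in the article).
- n = 14 per arm, or 11 after dropout (22/2).
- Three pairwise visit comparisons, so two-sided α = 0.05/3 = 0.0167 (assumed; the article does not count them).
- Error pooled over arms, df = 2n − 2. The critical t is 2.559 for n = 14 and 2.613 for n = 11.

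Formulas: SD of change = 30.79 × √(2(1 − r)); SE = SD of change/√n; noncentrality = loss/SE. The miss rate is the probability that a noncentral t stays inside the critical values.

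Example, n = 14, r = 0.5: SD of change = 30.79; SE = 30.79/√14 = 8.23. A 7 s loss gives noncentrality 7/8.23 = 0.85 and is missed 94% of the time.

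Miss rates within one arm, n = 14:

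| True loss | r = 0.5 | r = 0.7 | r = 0.8 | r = 0.9 |
|---|---|---|---|---|
| 7 s (lower end of the stated range) | 94% | 91% | 87% | 72% |
| 15.4 s (half an SD) | 73% | 54% | 34% | 6% |
| 23.5 s (midpoint of 7 and 40 s) | 38% | 14% | 3% | under 1% |
| 31.77 s (pilot difference) | 11% | 1% | under 1% | under 1% |

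With n = 11, a 15.4 s loss is missed 80%, 66%, 48% and 15% of the time across the same values of r. A 31.77 s loss is missed at most 22% of the time.

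Without Bonferroni (α = 0.05, n = 14), a 7 s loss is still missed 87% (r = 0.5) to 55% (r = 0.9) of the time. Low precision matters more here than the correction.

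The article uses the post-hoc P values only after a significant ANOVA effect. The calculation ignores that condition, which could only raise the miss rates.

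**Precision.** The 95% half-width for the within-arm change, n = 14, df = 26, t = 2.056, is 2.056 × 8.23 = 16.9 s at r = 0.5. At r = 0.9 the SE is 30.79 × √0.2/√14 = 3.68 s and the half-width is 7.6 s. For the between-arm difference in change, multiply by √2: 23.9 s and 10.7 s.

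**The case against.** The strongest reply is that the article contains no faulty decision rule. Nowhere does it say that a non-significant post-training versus 30-day comparison will count as maintenance, or that the arms will be judged one at a time, with one significant and the other not. A reader might infer either; the text supports neither. The planned group-by-time interaction is a proper guard against reading the arms separately. This part of the objection stands, so no error rate for a separate-arm reading is charged to the plan.

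Second, the hypothesis that tDCS prolongs the effect is a superiority question. Active versus sham at 30 days, or 30 days versus pretraining, can be answered by a difference test. That is correct, and only the stricter sense, no loss since the end of training, needs a criterion. But the objective asks whether the training results are maintained, and for that sense nothing suitable is stated.

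Third, the size depends on the loss considered. A reader might infer that a real loss would usually pass unnoticed. The table does not bear this out: a 23.5 s loss is missed 38% of the time or less, and larger losses rarely. A time effect pooled over both arms would do better still. With 28 participants and r = 0.5, SE = 30.79/√28 = 5.82 s, and a 15.4 s loss (noncentrality 2.65, df 26) is missed about 46% of the time instead of 73%. The reported intra- and inter-rater ICCs of 0.90 and 0.91 also make a high correlation plausible, though they concern reliability, not visits a month apart with training stopped between them.

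Last, a definition of maintenance could sit in a fuller analysis plan. That softens the point without removing it: the article does state its inferential method, and that method cannot answer this part of the main objective.

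**Conclusion.** The point holds in a limited form. The main objective asks about maintenance at 30 days, the stated tools test only for differences, and the ANOVA as written does not name the 30-day visit. Non-significance with 14 or 11 per arm cannot establish that the gain was kept. The weakness is large for small losses (7 s: missed 94% to 72% with 14 per arm), depends strongly on the correlation for moderate ones (15.4 s: 73% to 6%) and is minor for losses near the pilot difference (31.77 s: 11% or less).

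These figures rest on an SD of 30.79 s at every visit, r between 0.5 and 0.9, three Bonferroni comparisons and pooled error. It would go too far to say that the plan treats non-significance as maintenance, or that a real loss would usually be missed. What can be said is that the plan states no rule that could support a conclusion of maintenance. This should be corrected before the data are analysed.

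**What to change.** In the Data analysis section:

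1. Include the 30-day visit in the group-by-time analysis of Glittre-ADL time.
2. Report, for each arm, the change from post-training to 30 days with its 95% confidence interval.
3. State that a non-significant P value will not be read as maintenance.
4. Base any claim that tDCS prolongs the effect on the between-arm difference in that change, or in 30-day performance, with its confidence interval.
5. If a positive claim of maintenance is wanted, have the sponsor fix and justify a loss margin before unblinding. Claim maintenance only if the upper confidence limit of the loss lies below it, and otherwise report the result as inconclusive. The 7 to 40 s range is given for improvement, so using it for loss needs its own justification. The article also gives two minimal detectable changes, 0.40 min (24 s) and 0.07 min (about 4 s), so the sponsor should say which of them, if either, informs the margin.

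The cost is a few sentences, with no new data or visits. The drawback is that maintenance becomes harder to claim: with a within-arm half-width of about 8 to 17 s for 14 per arm, a margin near 7 s could rarely be met, and inconclusive may be the honest result.

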### Trial design

The study is a randomized, double-blind, placebo-controlled clinical trial. This study will follow the recommendations of the SPIRIT statement, whose checklist can be found in Additional file 1. The study was registered in the Brazilian Clinical Trial Registry (RBR-2crd42) and received approval from the Human Research Ethics Committee of University Nove de Julho, São Paulo, Brazil (process number 3.077.953).

## Methods

To participate in the study, elderly individuals who have the following eligibility criteria will be recruited from the community.

To be included, participants must be between 60 and 80 years old, sign an informed consent form, be able to independently stand and walk without a care device (i.e., be nonfrail elderly) as classified by the Physical Performance Test scale [24] and be hemodynamically stable (blood pressure <140 and 90 mmHg) according to the guidelines of the Brazilian Society of Cardiology [25].

Exclusion criteria include: experiencing amputation or immobilization of a lower limb; musculoskeletal conditions that would restrict the execution of training; chronic or progressive neurological conditions of central or peripheral origin that cause motor limitations; pain that impedes the execution of training and evaluation; diagnosis of acute coronary syndrome or severe heart condition (score >4 on the New York Heart Association functional classification [25]); presence of chronic obstructive pulmonary disease, asthma, cystic fibrosis, or interstitial lung disease; cognitive impairment with a score less than 26 literate and 13 illiterate in the Mini-Mental State Examination [26]; visual impairment that prevents training; pacemaker use; or any contraindication to the use of tDCS, such as history of seizure or recurrent epilepsy, tumor of the brain, metallic material near the stimulation site, skin infection or injury at the electrode application site.

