### Intervention

#### Multicomponent training

According to the American College of Sports [10], for physical activity to be considered multicomponent training, it must contain at least three components. Components can be activities based on coordination of movement, balance, flexibility, cardiorespiratory capacity, muscle endurance, agility and cognition.

Therefore, our multicomponent training protocol was based on these recommendations, and will be performed in the following sequence: 1) a warm-up period, during which the individual must walk along a straight and flat track of 20 m for 5 min; 2) a cardiorespiratory capacity component where the individual should ride a stationary exercise bike for 20 min; 3) a lower limb strength training component, where the individual should sit and stand up from a chair without support for the upper limbs for 5 min; 4) a balance component, where the individual should walk 10 m along a path that will contain obstacles to deflect them (zigzag in cones) and another 10 m walk on unstable surfaces (carpets of different thickness) and up and down two steps; the individual will perform these components for 10 min; 5) an upper limb strength training, coordination, balance, and cognition component, where the individual should transfer three balls, weighing 1 kg each, from an upper shelf (at shoulder level) to a lower shelf (at pelvis waist level) and then to the floor, and then return the objects to the top shelf in the same sequence for 10 min; and 6) a flexibility and cooling-down component, where the individual will perform stretching in the standing position and relaxation in the sitting position for 5 min.

The sessions will be individualized, lasting 50 min, and in the 20-min period of training on the bike tDCS will be applied.

The Karvonen formula (220 – age) [27] will be used to determine the maximum heart rate of each participant, considering effort on a submaximum test of 60% to 80% of predicted heart rate. Before initiating training, the exercises will be demonstrated to familiarize the participants with the procedures. The treatment will be performed twice a week for 12 weeks (for a total of 24 sessions).

The following variables will be measured before, during (if necessary) and after each multicomponent training session as a protective measure against possible risks: heart rate, respiratory rate, blood pressure, oxygen saturation and lower limb fatigue level [28].

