### Data collection methods

#### Evaluations to characterize the elderly participants

##### Fragility assessment

To characterize the elderly regarding fragility we will use the Physical Performance Test scale [24], which classifies the elderly as nonfragile (32 to 36 points), slightly fragile (25 to 31 points) or moderately fragile (17 to 24 points).

This scale scores the performance of nine tasks: 1) raise a book from waist height to a shelf above shoulder level; 2) put on and take off a coat (participants put on and take off an appropriately sized standard apron as quickly as possible); 3) participants retrieve a penny coin that is located in front of the foot as quickly as possible; 4) participants sit, stand fully, and sit back in a chair that has a seat height of 40 cm without using their hands five times as quickly as possible; 5) participants rotate clockwise and counterclockwise quickly, but safely, and are subjectively rated for stability and the ability to produce a rotating motion; 6) walking 15 m by walking 7 m in a straight line, turning, and returning to the initial starting place as quickly as possible and safely; 7) climb 10 flights of stairs one at a time as fast as possible; 8) participants climb four flights of stairs (one point is given for each flight of stairs completed); and 9) participants are scored according to their ability to keep their feet together for 10 s.

The score ranges from 0 to 4 for each task, with a maximum score of 36, being: 0 = impossible to complete; 1 = ends with difficulty, above 10 seconds; 2 = ends with difficulty in 10 seconds; 3 = ends safely over 10 seconds; and 4 = finishes safely in 10 seconds.

This Physical Performance Test scale was adapted into Portuguese by Mitre et al. [24]. The intraclass correlation (ICC) was 0.81 (95% confidence interval (CI) 0.51–0.93) for the reliability of the same examiner, and ICC was 0.86 (95% CI 0.63–0.95) for reliability between different examiners. Cronbach’s α coefficient was 0.89 and 0.92, respectively.

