### Trial status

At the time of manuscript submission, we were recruiting patients. This study was given the registration protocol RBR-2crd42 on 20 December 2018, updated on 3 July 2019. Recruitment commenced on 21 January 2019 and is expected to be completed on 30 July 2019. The study is expected to be completed by November 2019.

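### The New York Heart Association cut-off for the severe-heart-condition exclusion lies above the top of the scale, so as printed it excludes no class (minor; one-line correction)

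*Protocol article*

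**What the plan says.** The exclusion criteria in the Methods section of the protocol article cover two cardiac diagnoses together: "diagnosis of acute coronary syndrome or severe heart condition". A bracket follows the second and gives it a numerical definition: "severe heart condition (score >4 on the New York Heart Association functional classification". This is the only place where the article mentions that classification or gives any functional-class cut-off.

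Other eligibility items bear on cardiovascular fitness without setting a functional class. Participants must "be hemodynamically stable (blood pressure <140 and 90 mmHg"), must not have a pacemaker, and must stand and walk unaided and be nonfrail on the Physical Performance Test. The Fragility assessment section describes that test as one "which classifies the elderly as nonfragile (32 to 36 points), slightly fragile (25 to 31 points) or moderately fragile (17 to 24 points").

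On safety during training, the Multicomponent training section states: "The following variables will be measured before, during (if necessary) and after each multicomponent training session as a protective measure against possible risks". It also provides that a session stops at once if symptoms or signs suggest risk.

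**The concern.** The bracket is there to turn a verbal criterion into one that screening staff can apply in the same way to every candidate. A threshold above the highest value of the scale cannot do that. Taken literally, a class IV candidate fails to meet the number given for exclusion, so the number contradicts the words that it defines.

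This is a safety criterion in an exercise trial, so it should be usable. Participants are 60 to 80 years old and attend 24 sessions, each with 20 minutes on a stationary bike. The training intensity is set by "considering effort on a submaximum test of 60% to 80% of predicted heart rate". At stake is consistent screening of people with heart disease, in particular how a class III candidate would be handled by two screeners who each repaired the misprint in their own way. No statistical quantity is at stake.

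**Working it through.** The article gives no derived figure to reproduce. The check applies the printed rule to each value of the scale and then looks for anything in the article that would correct it.

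**Inputs**
- Printed rule: score above 4 (Methods, exclusion criteria).
- Scale: classes I, II, III and IV, coded 1, 2, 3 and 4. The article does not print this range. It is taken as an assumption because it defines the instrument that the article names.

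**Step 1. Apply the rule and its plausible corrections**

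| Rule | Classes meeting it | Number out of 4 |
|---|---|---|
| score > 4 (as printed) | none | 0 |
| score ≥ 4, or equally > 3 | IV | 1 |
| score ≥ 3, or equally > 2 | III and IV | 2 |

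The maximum is 4, and 4 > 4 is false, so the printed rule selects an empty set.

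**Step 2. Look for a correction elsewhere.** There is none. The Fragility assessment and Depression scale sections, which describe how participants are characterised, do not mention functional class.

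**Step 3. Which correction is closest to the text?** The printed digit is 4 and the word attached to it is severe. Changing only the inequality sign, from > to ≥, gives class IV. Reaching class III needs a different digit, and nothing in the article points to it. Class IV is therefore the minimal correction, but the article does not settle what was intended.

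**Step 4. What still screens a candidate if the number is ignored?**

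| Safeguard | Section | Sets a functional class? |
|---|---|---|
| The words severe heart condition | Methods | No, but they still exclude |
| Acute coronary syndrome | Methods | No |
| Pacemaker | Methods | No |
| Blood-pressure limit | Methods | No |
| Unaided walking and nonfrail status (32 to 36 of 36 points) | Methods; Fragility assessment | No |
| Vital signs around each session; stop at any sign of risk | Multicomponent training | No |

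None of these supplies the missing cut-off, but together they leave little for a corrected class IV threshold to add. If class IV is taken to mean symptoms even at rest (again the scale's own definition, not printed in the article), few such candidates, and perhaps none, would walk unaided and score 32 or more on physical tasks, most of them performed at speed. The number of candidates affected cannot be derived from the article.

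**The case against.** The strongest reply is that this is a one-character misprint. The words still exclude a severe heart condition when the bracket is unusable, and any clinician would read the digit as class IV. Under that reading the correction would change the eligibility of almost no one. The article also condenses a fuller protocol that is not shown, and that protocol may carry the right number. Finally, the four-class range is outside the document.

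Most of this stands as an argument about weight, and it is why the point is minor. It does not remove the error. The threshold is wrong in the text as published, which is a misstatement and not a detail left to another document. The range of the scale is part of the definition of an instrument that the article itself names, not a result recalled from a cited study. Class IV is the likeliest intention, but the article does not confirm it.

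A reader might infer more in three ways, and the article supports none of them.
- That people with severe heart failure were, or would be, enrolled. This does not follow, because the verbal criterion and the other safeguards still operate, and nothing shows that screeners applied the inequality literally.
- That class III was meant to be excluded. No text indicates this; it is a clinical question for the investigators.
- That participants already enrolled must be re-screened. The trial status section says "Recruitment commenced on 21 January 2019 and is expected to be completed on 30 July 2019", so some had probably been enrolled when the article was written. That alone does not show that anyone was wrongly admitted.

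**Conclusion.** The error is real and its severity is minor. As printed, the New York Heart Association threshold excludes 0 of 4 classes and contradicts the criterion that it is meant to define. The class IV reading excludes 1 of 4 and a class III reading 2 of 4. The conclusion rests on one assumption, that the scale runs from I to IV. That the practical effect is small rests on the other criteria and the session monitoring being applied as described. The sample size of 28, the planned analysis and the randomised comparison do not depend on this threshold.

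**What to change.** In the exclusion criteria, replace the score above 4 with class IV (score ≥ 4) on the New York Heart Association functional classification. Ask the clinical investigators to confirm whether class III was also meant; if so, print class III or IV (score ≥ 3).

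The choice carries a trade-off. Class IV alone stays closest to the text and leaves class III candidates eligible. Adding class III is more protective for training at this intensity but may cost a few screen failures in a 28-person trial.

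The cost is one line of text and one confirmation. Sample size and analysis do not change. Because recruitment had begun, the team may also choose to look at the screening records of those enrolled (at most 28 if the planned size is kept) against the confirmed cut-off. This is optional.
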